### Study Procedures

Centers that do not adopt any standardized procedure for the application of PPS and/or IBS are selected for the study. These centers are then randomized in a 1:1 ratio to the experimental and control arms of the study. Eligible patients in centers randomized to the experimental group are evaluated within 48 hours from hospital admission by using Padua Prediction Score and IMPROVE Bleeding Score. Centers randomized to the control group evaluate eligible patients according to clinical judgement and current clinical practice. In order to minimize any study bias, it is strongly recommended that health care personnel not involved in the patient's clinical evaluation fills the study-specific electronic case report form. All patients, irrespective of allocation arm, are assessed at a 90-day follow-up in order to evaluate the occurrence of thrombotic, hemorrhagic, or other major clinical events (deaths, cardiovascular events), and the use of VTE prophylaxis.

Study duration was originally set to 1 year. However, due to coronavirus disease 2019 pandemic, the study frame was extended to additional 2 years in order to achieve the needed sample size.

Formal approval from the Ethics Committee (EC) of the participating Centers will be obtained before any study procedure.

#### Observation and Measurements

For each enrolled patient, the following information during the hospital stay is collected: age, sex, height, and body weight (to compute body mass index), comorbidities, past medical history (with special consideration for history of VTE and recent [i.e., <3 months] history of bleeding), functional status (chronically bedridden, reduced mobility, support of a caregiver), antithrombotic and/or hormonal therapies, laboratory tests (in particular hemoglobin, platelet count, creatinine clearance), occurrence of objectively confirmed venous thromboembolic events and/or major bleeding events (according to International Society on Thrombosis and Haemostasis criteria), any other clinically relevant events, Padua Prediction Score and IMPROVE Bleeding Score (for the experimental group only), and outcome of hospitalization (discharge, transfer to another unit, death).

All patients are evaluated after 90 days through a telephone call or during an outpatient visit, if planned. The following information is collected: patient status (survival or death, in the latter case date and possible cause of death should be recorded), occurrence of objectively confirmed venous thromboembolic events and major bleeding, any other clinically relevant event, possible rehospitalization and related cause, and current antithrombotic therapies, if any. Clinical records relevant to venous thromboembolic events and major bleedings will be made available to an independent Adjudication Committee for evaluation.

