Simplified Geneva Risk Score	Blondon et al	Prospective cohort study (for validation)	9
Padua Prediction Score	Barbar et al.	Prospective cohort study	8
	Vardi et al	Prospective cohort study (for validation)	18
IMPROVE VTE	Spyropoulos et al	Prospective cohort study	17
	Rosenberg et al	Case–control study (for validation)	15
	Mahan et al	Retrospective cohort study (for validation)	34
	Greene et al	Retrospective, cohort study (for validation)	35
Kucher RAM	Kucher et al	Randomized controlled study	13
	Woller et al	Retrospective cohort study (for validation)	19
MITH RAM	Zakai et al	Retrospective cohort study	20
*Bleeding RAM*			
IMPROVE Bleeding	Decousus et al	Prospective cohort study	11
	Hostler et al	Prospective cohort study (for validation)	12
	Rosenberg et al	Prospective cohort study (for validation)	16

Abbreviations: IMPROVE, International Medical Prevention Registry on Venous Thromboembolism; MITH, Medical Inpatients and Thrombosis; RAM, risk assessment model; VTE, venous thromboembolism.

More recently, in the real-world Federazione delle Associazioni dei Dirigenti Ospedalieri Internisti (FADOI)-NoTEVole (Studio nazionale, osservazionale retrospettivo, sul pattern prescrittivo della profilassi del tromboembolismo venoso in Medicina Interna alla dimissione) study, almost half of the patients admitted to IM division carried a high thrombotic score according to Padua Prediction Score, but only 7.2% presented a high bleeding risk according to IMPROVE Bleeding Score.
21
These results suggest that VTE prophylaxis can be prescribed to a large number of hospitalized, medical patients with very limited harm.

Poor evidence is available comparing the use of a RAM versus clinical judgement in choosing whether or not to prescribe VTE prophylaxis. In a single-center, prospective, quasi-randomized study, the adoption of Padua Prediction Score was associated with a 50% reduction in the incidence of VTE (either symptomatic or asymptomatic) compared with clinical judgement, with no differences in terms of bleeding and death from all cause.
12
These preliminary results need a confirmation in a large, multicenter study in order to test the appropriateness of VTE prophylaxis through a systematic application of RAMs, and to compare it with clinical judgement.

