## Study Rationale and Methods

### Trial Design and Objectives

FADOI promoted the Reducing Important Clinical Outcomes in hospitalized medical ill patients (RICO) study, a multicenter, cluster-randomized, controlled clinical trial (ClinicalTrials.gov Identifier: NCT04267718) involving a large number of IM divisions affiliated to FADOI across the whole Italian territory. The aim was to evaluate the systematic use of RAMs, that is, Padua Prediction Score (PPS) and IMPROVE Bleeding Score (IBS), compared with clinical judgement as a guide for prescribing VTE prophylaxis, and the relevant clinical outcomes (thromboembolic and hemorrhagic events).

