### Study Endpoints

The primary endpoint of the study is to assess the efficacy of a systematic evaluation of the thromboembolic and bleeding risk in reducing the composite rate of thromboembolic and hemorrhagic events in hospitalized, acutely ill medical patients at a 90-day follow-up.

Secondary endpoints include (i) the evaluation of clinical outcomes (VTE, major bleeding, cardiovascular events) at the time of hospital discharge (i.e., discharge at home, transfer to another unit, or death) and (ii) the assessment of VTE prophylaxis prescription during hospital stay and at the time of discharge.

As thromboprophylaxis has been shown to have the potential to reduce arterial events as well,
22
23
24
25
information about arterial events (e.g., stroke, acute myocardial infarction, peripheral artery disease) has been collected and will be analyzed as an exploratory outcome.

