#### Definition of the Control Group

This group includes those centers randomized to evaluate VTE prophylaxis in all eligible patients based on clinical judgement only.

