#### Statistical Analysis

Data will be analyzed and reported using the Consolidated Standard of Reporting Trials and the International Conference on Harmonisation E9 guidelines. All primary analyses will be on an intention-to-treat basis including all randomized participants.

Baseline characteristics, collected at the time of enrollment, will be cross-tabulated, according to the randomized group to check for appropriate balance and provide an overview of the study population. Baseline characteristics will be summarized as mean and standard deviation for continuous variables and as frequencies and percentages for categorical ones.

The primary outcome (proportion of thromboembolic and hemorrhagic events at a 90-d follow-up after hospital discharge) will be analyzed through an univariate logistic regression analysis to check for variables differing between groups. Variables significant at
*p*
≤ 0.10 will be included as covariates in the multilevel logistic regression model that takes into account the clustered nature of the data. As RICO is a randomized trial, we do not have a priori potential confounders. A propensity score analysis as an additional sensitivity analysis will be also performed. Considering the potential risk of an unbalanced recruitment across participating centers, the use of a multilevel logistic regression model is solid in case of unequal cluster size.
27
Secondary outcomes will be compared between groups and follow the approach detailed above for primary outcome.

Numbers and percentages of adverse events (AEs) and serious AEs will be cross-tabulated with allocated group. According to the study protocol and the primary outcome of the study, thromboembolic and hemorrhagic events will not be considered AEs.

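### Both risk scores are recorded in the experimental arm only and not derived for controls, so the secondary comparison of prophylaxis prescription is not related to risk

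*Protocol article*

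**What the plan says.** Under Trial Design and Objectives, the protocol article sets out to evaluate systematic use of the Padua and IMPROVE Bleeding scores "compared with clinical judgement as a guide for prescribing VTE prophylaxis", together with clinical outcomes. The Introduction says a large multicenter study is needed "to test the appropriateness of VTE prophylaxis through a systematic application of RAMs, and to compare it with clinical judgement".

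Study Endpoints lists as a secondary endpoint "the assessment of VTE prophylaxis prescription during hospital stay and at the time of discharge". Statistical Analysis adds: "Secondary outcomes will be compared between groups and follow the approach detailed above for primary outcome". That approach is univariate screening at p ≤ 0.10, then a multilevel logistic model, with a propensity score analysis as sensitivity analysis.

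Observation and Measurements lists the data for each enrolled patient and limits one item: "Padua Prediction Score and IMPROVE Bleeding Score (for the experimental group only". The control arm consists of "centers randomized to evaluate VTE prophylaxis in all eligible patients based on clinical judgement only". The same list collects age, body mass index, comorbidities and history of thrombosis and bleeding without restriction by arm, as well as "functional status (chronically bedridden, reduced mobility, support of a caregiver), antithrombotic and/or hormonal therapies, laboratory tests (in particular hemoglobin, platelet count, creatinine clearance".

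**The concern.** The scores are meant to redirect prophylaxis: towards patients at high thrombotic and low bleeding risk, and away from the rest. To see whether they do so better than clinical judgement, prescription has to be set against risk in both arms. As described, only the experimental arm has the scores, so what remains between arms is a comparison of prescription as such.

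That comparison is hard to read in any direction. The Introduction stresses under-prescription, which makes a higher rate look like success. The Discussion cites a before-after study in which use fell from 56.7% to 43.3% after the scores were introduced, with the incidence of thrombosis unaffected, and treats this as a safe saving. An equal rate could be taken as no change in practice when treatment had in fact moved from lower-risk to higher-risk patients. At stake are the meaning of this secondary endpoint and the ability to explain the primary result, above all a null one. In addition, the score totals would not be available for both arms in the baseline table.

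**Working it through.** **Text check.** Definition of the Control Group and Study Procedures give controls clinical judgement only. Observation and Measurements restricts the scores to the experimental arm. No section derives them for controls, at the site or centrally. Study Endpoints names prescription without a risk category, and Statistical Analysis names no score or stratum. Covariate screening and the propensity score could bring in single risk factors, but they adjust for imbalance; they do not show who was treated at which level of risk.

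**Illustration.** The plan has no figure of its own to reproduce here. Inputs:
- Patients per arm: 2,844 / 2 = 1,422 (Sample size; the total is stated after allowing for 5% dropout, so analysed counts would be somewhat lower).
- High thrombotic risk: "almost half of the patients admitted to IM division carried a high thrombotic score according to Padua Prediction Score", read as 0.50. High bleeding risk: 7.2%, same study.
- Indicated means Padua ≥4 with IMPROVE Bleeding <7, the cut-offs in the Introduction.
- pe and pn, the shares of indicated and of other patients treated in the control arm, are assumed. The Introduction reports 40 to 75% of eligible patients treated, without saying that eligible means indicated by these scores. It gives nothing for the others.

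Indicated share, assuming independence: I = 0.50 × (1 − 0.072) = 0.464. Without independence it lies between 0.50 − 0.072 = 0.428 and 0.500.

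Overall rate: R = I × pe + (1 − I) × pn. Decisions against the scores: D = 1,422 × [I × (1 − pe) + (1 − I) × pn]. Full score-following gives R = 46.4% and D = 0. A control arm has the same R when pn = I × (1 − pe) / (1 − I).

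| Controls treat (indicated / others) | R | Gap from 46.4% | D of 1,422 |
|---|---|---|---|
| 60% / 34.6% (solved to match) | 46.4% | 0 | 528 |
| 75% / 21.6% (solved to match) | 46.4% | 0 | 330 |
| 75% / 20% | 45.5% | 0.9 points | 317 |
| 60% / 40% | 49.3% | 2.9 points | 569 |
| 40% / 40% | 40.0% | 6.4 points | 701 |
| 60% / 10% | 33.2% | 13.2 points | 340 |

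The first row in full: pn = 0.464 × 0.40 / 0.536 = 0.346; D = 1,422 × 2 × 0.464 × 0.40 = 528. With I from 0.428 to 0.500, the two matched rows become 487 to 569 and 304 to 356.

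**Imperfect adherence.** If experimental sites treat 90% of indicated and 10% of other patients, R = 0.464 × 0.90 + 0.536 × 0.10 = 47.1% and D = 142. Controls at the same R have D = 538 (pe 0.60, pn 0.360) or 340 (pe 0.75, pn 0.230), that is 396 or 198 more.

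**A different case mix.** The Introduction also cites a cohort with more than three-fourths at high thrombotic risk, almost 90% of them at low bleeding risk: I is about 0.75 × 0.90 = 0.675. At pe 0.60, equal rates then need pn = 0.675 × 0.40 / 0.325 = 0.83, above pe, which is implausible. At pe 0.75 they need pn = 0.675 × 0.25 / 0.325 = 0.52.

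**Strata per arm for the proposed analysis** (I = 0.464): indicated 1,422 × 0.464 = 660; Padua <4, 1,422 × 0.50 = 711; Padua ≥4 with Bleeding ≥7, 1,422 × 0.50 × 0.072 = 51, or 51 / 16 = 3.2 per center.

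**The case against.** The restriction itself is right. Scoring controls at the bedside would contaminate the comparison, and the fix leaves it in place. The risk data are collected for every patient, nothing forbids later derivation, and derived variables and strata are often left to an analysis plan, which is not at hand and may provide them. No endpoint is worded as appropriateness; that term stands only in the Introduction. All of this stands, and it lowers the priority. It does not remove the point: the article states an experimental-only rule rather than staying silent, and an analyst would not clearly read a both-arm derivation into it.

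The matched scenarios are also open to challenge. Their pn values were solved to make the arms equal, and no document supports any rate among non-indicated patients. Where under-prescription is marked, as in the last two rows of the table, the overall rate does show a gap. A reader might infer that the endpoint will conceal the effect of the scores; the documents support only that it can.

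Finally, derived scores have limits. The data are gathered over the hospital stay, whereas bedside scores date from the first 48 hours, and prescription is also assessed at discharge. The fix has to deal with this timing.

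**Conclusion.** The point holds as a modest improvement to one secondary endpoint. As written, prescription is compared between arms without relation to thrombotic or bleeding risk, although the stated need and aim concern scores against judgement as a guide to prescribing. The possible masking ranges from substantial (528 of 1,422 control decisions against the scores at an equal overall rate) to little (a 13-point gap in plain view). Which applies depends on control prescribing rates that the article does not give. The counts further assume 50% at high thrombotic risk, 7.2% at high bleeding risk and, except for the stated bounds, independence of the two.

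Two stronger inferences are not supported. A reader might conclude that a risk-related comparison is impossible; it is only unplanned, since risk-factor, functional and laboratory data are collected in both arms. A reader might also conclude that the trial's main result is compromised; the primary intention-to-treat comparison does not use the scores and is unaffected.

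**What to change.** Keep bedside scoring in the experimental arm only. Amend Observation and Measurements so that both scores are also derived centrally in both arms, by one algorithm, from case report form items dated within 48 hours of admission, after data collection and without feedback to control sites. Then:
- Show the derived scores by arm in the baseline table.
- Beside the overall rate, compare in-hospital prescription between arms within Padua ≥4 with Bleeding <7 and within Padua <4, using the planned multilevel model with an arm-by-stratum term. Report Padua ≥4 with Bleeding ≥7 descriptively, given its size.
- Treat discharge prescription by admission stratum as descriptive.
- Report concordance with the scores as adherence only, not as proof of better care.
- Check derived against bedside scores in the experimental arm, and report missing score items by arm.

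Treatment, sample size and primary analysis do not change. The article does not list the components of the scores, so first confirm that the case report form captures and dates each one. The downside is that control scores are retrospective. Some items may be missing, and experimental sites, prompted by the scores, may record risk items more fully; hence the last check.

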#### Safety Procedures

All drugs used in this study are part of the standard-of-care according to the indications specified in the marketing authorization. The report of a suspected adverse reaction to these drugs in patients enrolled in the study is collected and reported based on current laws (D.M. April 30, 2015, as a transposition of European directives 2010/84/UE e 2012/26/UE) by filling a report form of suspected adverse reaction within the time specified by the law.

The report form can be filled electronically by accessing the platform Vigifarmaco (
www.vigifarmaco.it
) through the guided procedure, manually by paper or by fax or e-mail to the Local Pharmacovigilance Manager of the hospital. In addition, a copy of the form must be emailed or faxed to the study promoter.

### Ethical Considerations

This study is conducted in compliance with the protocol and in accordance with Centro Studi Fondazione FADOI standard operating procedures. These are designed to ensure adherence to Good Clinical Practice, International Conference on Harmonization Harmonized Tripartite Guidelines for Good Clinical Practice and Declaration of Helsinki.
26

#### Institutional Review Board/Ethics Committee

Before implementing this study, the protocol, the proposed informed consent form, and any other information relevant to enrolled subjects were reviewed by the Institutional Review Board (IRB)/EC of the participating centers. A signed and dated statement confirming that the protocol and the informed consent were approved by the IRB/EC of the participating center was sent to Centro Studi Fondazione FADOI before study initiation.

#### Informed Consent

The investigator must explain to each subject (or legally authorized representative) the nature of the study, its purpose, the procedures, the expected duration, the potential risks and benefits involved, and any discomfort it may entail. Each subject must be informed that participation in the study is voluntary and that he/she may withdraw his/her consent for the study at any time. Consent withdrawal will not affect his/her subsequent treatment or relationship with the attending physician. This informed consent is given by means of a standard written statement in nontechnical language. The subject should read and consider the statement before signing and dating, and should be given a copy of the signed document. If written consent is not possible, oral consent can be obtained if witnessed by a signed statement from one or more people not involved in the study. It should also be mentioned why the patient was unable to sign the form. No subject can enter the study before his/her informed consent has been obtained.

### Statistical Considerations

#### Sample size

In order to demonstrate a 50% reduction in the proportion of the primary outcome in the experimental group and assuming an incidence of the primary outcome of 3.5% in the control group at 90 days, 16 clusters of at least 90 patients for each group are needed to have a fixed number of equal-sized randomized clusters, with 80% power at a 5% significance level (two-sided) and with an intracluster correlation coefficient of 0.001. Considering a potential dropout rate of 5%, at least 32 centers for a total of 2,844 patients are required for the study.

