**Methods**
 Reducing Important Clinical Outcomes in hospitalized medical ill patients (RICO) is a multicenter, cluster-randomized, controlled clinical trial (ClinicalTrials.gov Identifier: NCT04267718). Acutely ill patients hospitalized in Internal Medicine wards are randomized to the use of RAMs—namely the Padua Prediction Score and the International Medical Prevention Registry on Venous Thromboembolism Bleeding Score—or to clinical judgement. The primary study outcome is a composite of symptomatic objectively confirmed VTE and major bleeding at 90-day follow-up. Secondary endpoints include the evaluation of clinical outcomes at hospital discharge and the assessment of VTE prophylaxis prescription during the study period. In order to demonstrate a 50% reduction in the primary outcome in the experimental group and assuming an incidence of the primary outcome of 3.5% in the control group at 90-day; 2,844 patients across 32 centers will be included in the study.

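### The total of 2,844 patients, presented as allowing for 5% dropout, is below the plan's own pre-dropout minimum of 32 × 90 = 2,880

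*Protocol article*

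**What the plan says.** The Sample size section of the protocol article gives the inputs and two size targets.

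- Control rate: "assuming an incidence of the primary outcome of 3.5% in the control group at 90 days".
- Effect: "In order to demonstrate a 50% reduction in the proportion of the primary outcome in the experimental group", which implies 1.75% in the experimental group.
- Error rates: 80% power at a two-sided 5% level.
- Clustering: "with an intracluster correlation coefficient of 0.001".
- First target, given as the condition for that power: "16 clusters of at least 90 patients for each group are needed to have a fixed number of equal-sized randomized clusters".
- Second target, given after the dropout allowance: "Considering a potential dropout rate of 5%, at least 32 centers for a total of 2,844 patients are required for the study".

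The Methods paragraph of the Abstract carries the second target as the trial's size: "2,844 patients across 32 centers will be included in the study". Nothing else in the article links the two figures.

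**The concern.** The first target multiplies out to 2 × 16 × 90 = 2,880 as a minimum. The second should be that number raised to absorb a 5% loss, but it is 36 patients lower. Spread over 32 centres, 2,844 is 88.9 per centre, so the stated minimum of 90 is missed on average even if nobody drops out.

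A reader cannot tell whether the recruitment target is 2,844, 2,880 or something above 3,000, nor whether 80% power is meant to hold before or after dropout. The allowance also has a concrete purpose: the section on dropout criteria removes patients who start a new anticoagulant treatment in hospital, and the primary outcome depends on a 90-day contact.

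**Working it through.** **Inputs (all from Sample size):** p1 = 0.035, p2 = 0.0175, two-sided α = 0.05, power 80%, ICC = 0.001, k = 16 clusters per arm, m = 90, dropout 5%.

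**1. Unclustered size per arm.** Unpooled formula: n = (1.960 + 0.842)² × [p1(1 − p1) + p2(1 − p2)] / (p1 − p2)² = 7.849 × 0.05097 / 0.00030625 = 1,306.3. With the pooled variance under the null, n = 1,310.

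**2. The stated 90 per cluster reproduces.** With k fixed, m = n(1 − ICC) / (k − n × ICC).
- Pooled: 1,310 × 0.999 / (16 − 1.310) = 89.1, rounded up to 90.
- Unpooled: 1,306.3 × 0.999 / (16 − 1.306) = 88.8.

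So 90 per cluster is the requirement before any dropout, and 32 × 90 = 2,880.

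**3. The stated 2,844 is the size of a total without dropout.** The design effect at m = 90 is 1 + 89 × 0.001 = 1.089.
- Unpooled: 2 × 1,306.3 × 1.089 = 2,845.
- Pooled: 2 × 1,310 × 1.089 = 2,853.

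**4. What a 5% allowance would give.**
- From 2,844: 2,844 / 0.95 = 2,994.
- From 2,880: 2,880 / 0.95 = 3,032.
- Per centre: 90 / 0.95 = 94.7, so 95, and 32 × 95 = 3,040.

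**5. Power with equal clusters.** Effective n per arm = (N/2) / [1 + (N/32 − 1) × 0.001]; power from the normal approximation.

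| Evaluable N | Per centre | Power (pooled / unpooled) |
|---|---|---|
| 2,880 | 90.0 | 80.4% / 80.5% |
| 2,844 | 88.9 | 79.9% / 80.0% |
| 2,702 (2,844 × 0.95) | 84.4 | 78.1% / 78.1% |

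In detail for the last row (unpooled): design effect 1.0834; effective n = 1,350.9 / 1.0834 = 1,246.9; SE = √(0.05097 / 1,246.9) = 0.00639; 0.0175 / 0.00639 = 2.737; power = Φ(2.737 − 1.960) = 78.1%.

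A t reference with 30 degrees of freedom lowers every row (77.9% at 90 per centre, 75.4% at 84.4), with a drop of similar size. The normal approximation is used here because it reproduces the plan's 90 per cluster at 80% power.

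**The case against.** **The cause is not established.** A reader might infer from step 3 that the 5% inflation was announced and then forgotten. The document does not support that as a fact, because several routes lead to 2,844:
- The unpooled route gives 2,845, or 2,846 if each arm is rounded up, and reaches 2,844 only by rounding down.
- A continuity-corrected calculation with no clustering gives exactly 2 × 1,422 = 2,844.
- One route includes dropout: 1,310 × 1.031 = 1,350.6, rounded to 1,351; 2 × 1,351 / 0.95 = 2,844.2. Its design effect of 1.031 = 1 + (32 − 1) × 0.001 uses the number of clusters where the cluster size belongs, so it contradicts the stated 90.

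This part of the objection stands, and the point does not depend on the cause. No route found gives 2,844 with both the stated cluster size and the stated dropout. The arcsine formula comes closest, at 2,910 to 2,919 after dropout. That still exceeds 2,844, and the formula needs only 87 per cluster; its power at 2,702 evaluable is 79.2%.

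**The figures are minimums.** The words 'at least' attach to the 90 patients and to the 32 centres, so filling every centre to its minimum would give 2,880 or more. That softens the consequence. It does not reconcile the numbers, since the Abstract gives 2,844 without qualification.

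**Unequal centres.** The Statistical Analysis section foresees uneven recruitment ("Considering the potential risk of an unbalanced recruitment across participating centers"), and a reader might infer a power of 75% to 77%. Those values need assumed coefficients of variation of cluster size of 1.0 and 0.6; an assumed 0.3 gives 77.9%. The document states no such coefficient. Equal clusters are an openly stated planning assumption, and the multilevel model accommodates unequal sizes, though it does not restore power. The direction is certain and the amount is not, so this adds no weight here.

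**Conclusion.** Wrong as written; should be fixed. The total of 2,844 is 36 below the 2,880 in the preceding sentence and about 150 to 196 below a total that allows for 5% dropout (2,994 to 3,040).

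On the stated inputs and with equal clusters, 2,844 supports about 80% power only if every patient is evaluable; at the plan's own dropout rate it supports about 78%. A reader might conclude that the trial is seriously underpowered. The figures do not show that: the shortfall is about two points, and the estimand, the analysis and the validity of the inference are untouched. The contradiction itself is certain, since it needs only multiplication. The power figures rest on the normal approximation, the stated ICC and equal cluster sizes. Unequal centres would lower them somewhat further, by an amount that depends on a coefficient of variation the document does not give.

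**What to change.** Print one consistent set of figures in the Sample size section and the Abstract, and say whether each is enrolled or evaluable. There are two ways:

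1. **Keep 2,844 enrolled.** State that about 2,702 are expected to be evaluable after 5% dropout (about 84 per centre) with about 78% power, and bring the per-centre minimum of 90 into line, since 2,844 is about 89 enrolled per centre. This costs a text correction only.
2. **Keep 90 evaluable per centre.** State about 95 enrolled per centre, about 3,032 to 3,040 in total, which restores 80.4% to 80.5% power after 5% loss. This costs 188 to 196 more patients, about six per centre.

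If recruitment cannot be extended, only the first is open. In either case, add a sentence that the power assumes equal clusters and would be somewhat lower with unequal ones. Give a number only if the sponsor can supply a coefficient of variation from its own recruitment figures.
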